## Abstract

**Background:**

Envenomation caused by multiple stings from Africanized honeybees *Apis mellifera* constitutes a public health problem in the Americas. In 2015, the Brazilian Ministry of Health reported 13,597 accidents (incidence of seven cases per 100,000 inhabitants) with 39 deaths (lethality of 0.25%). The toxins present in the venom, which include melittin and phospholipase A_2_, cause lesions in diverse organs and systems that may be fatal. As there has been no specific treatment to date, management has been symptomatic and supportive only.

**Methods:**

In order to evaluate the safety and neutralizing capacity of a new apilic antivenom, as well as to confirm its lowest effective dose, a clinical protocol was developed to be applied in a multicenter, non-randomized and open phase I/II clinical trial. Twenty participants with more than five stings, aged more than 18 years, of both sexes, who have not previously received the heterologous serum against bee stings, will be included for 24 months. The proposed dose was based on the antivenom neutralizing capacity and the number of stings. Treatment will be administered only in a hospital environment and the participants will be evaluated for a period up to 30 days after discharge for clinical and laboratory follow-up.

**Results:**

This protocol, approved by the Brazilian regulatory agencies for ethics (National Commission for Ethics on Research – CONEP) and sanitation (National Health Surveillance Agency – ANVISA), is a guideline constituted by specific, adjuvant, symptomatic and complementary treatments, in addition to basic orientations for conducting a clinical trial involving heterologous sera.

**Conclusions:**

This is the first clinical trial protocol designed specifically to evaluate the preliminary efficacy and safety of a new antivenom against stings from the Africanized honeybee *Apis mellifera*. The results will support future studies to confirm a new treatment for massive bee attack that has a large impact on public health in the Americas.

## Background

African *Apis mellifera scutellata* bees were introduced into the southeastern region of Brazil in 1956. Twenty-six queens swarmed and initiated the Africanization of the American continent. These new hybrids, known as Africanized honeybees, are very defensive and attack *en masse*, causing serious injuries in humans and other animals. These bees have expanded their range and today are found from Argentina to the United States of America [1, 2]. Consequently, public health authorities in Brazil included bee sting events as an object of epidemiological vigilance as a consequence of the growing number of victims and of deaths related to this envenomation.

A recent epidemiological study made it possible to specify the factors concerning the incidence and severity of bee stings in Brazil [3]. They represented 6% of cases of envenomation and 9% of deaths due to animal envenomation, which denotes a high severity of bee stings. The incidence predominated in southern Brazil. Stings frequently occurred during recreational and professional activities, both in suburban and rural settings, and this explained why the incidence was fairly distributed for all ages, although the masculine gender was more involved. However, two thirds of the patients stung by bees arrived at the hospital less than three hours after the bee stings, which is very different from all other envenomated patients who arrived significantly later. Asymptomatic and mild envenomation accounted for up to 90% of cases, moderate envenomation for 10–18% and severe ones for 0.8–1.3%. The case fatality rate was 0.3 to 0.4% in all regions. Nevertheless, the study does not specify whether it was single or multiple punctures, i.e. it cannot be determined whether death is related to anaphylactic shock or envenomation after inoculation with a large amount of bee venom.

In 2000, 1,440 cases, including three deaths, were reported; in 2015 this number grew to 13,597 cases with 39 deaths, that is, an increase of almost tenfold in the number of cases in 15 years [3, 4]. Despite this impressive increase in reported incidence and mortality, many regional specialists believe that these numbers remain underreported. Fig. 1 below demonstrates this growth.

**Fig. 1 Fig1:**
[figure not shown]
Temporal distribution of the number of cases reported for Africanized honeybee sting in Brazil between 2000 and 2015 [4]

The physiopathology of this accident is complex due to the interaction between the diverse toxic components of the venom, the potential target organs and the immune response of the victim [5, 6]. Generally, bee stings can present two different outcomes:Anaphylaxis: occurs in individuals allergic to bee venom. In these cases a single sting can cause serious generalized allergic reactions, possibly leading to death. These consequences are not related to the toxicity of the venom due to the small quantity inoculated. Treatment is limited to general measures and the use of symptomatic drugs aiming to control the anaphylaxis [7].Direct toxicity from the venom: occurs when there are a substantial number of stings – generally more than 200 in adults. In this case, the venom volume is sufficient to cause damage to vital organs. Prominent among the toxic components are melittin and phospholipase A_2_, whose presence accounts for more than 60% of the dry weight of the venom. Direct injury to the cardiovascular, muscular, neurological, dermatological, metabolic, hematological, respiratory and renal systems can lead to death [7, 8].

The clinical manifestations resulting from multiple stings are: generalized pain, intense pruritus, flushing, hyperthermia, papules, urticarial plaques, hypotension, tachycardia, headache, nausea, vomiting, abdominal colic, bronchospasms and psychomotor agitation, which may subsequently evolve to a state of torpor, accompanied by respiratory and cardiac failure and, principally, severe renal failure [8–10]. The most common laboratory alterations are: leukocytosis with neutrophilia, hemolysis, thrombocytopenia, disseminated intravascular coagulation, rhabdomyolysis with increase of creatine phosphokinase (CPK), elevation of the enzymes aspartate aminotransferase (AST) and alanine amino transferase (ALT), increase of urea, creatinine and myoglobin in the urine [8–10].

Mortality is elevated at the extremes of age [4]. In children, due to lower body mass, envenomation can be much more severe, since with many stings the concentration of the toxic components is elevated. In the elderly, greater risk involves such preexisting comorbidities as chronic renal, cardiac or respiratory failure. These constitute an important additional risk factor in patients who are victims of multiple stings.

Given that until the present there has been no specific treatment, a consortium of Brazilian researchers developed the first antivenom for bee stings constituted of heterologous antibodies against the toxins from the venom and approved for clinical trial. In order to bridge the gap between the laboratory workbench and the patient, the objectives of this study were to standardize a clinical protocol applicable to patients affected by multiple stings from Africanized *Apis mellifera* honeybees, to evaluate safety and preliminary efficacy, and to standardize the lowest dose of the new antivenom. The absence of a previous standardized clinical protocol justifies its publication in order to open a discussion on the relevance of antivenom strategy and methodology proposed.

## Methods

### Antivenom development and dose proposal

Researchers from the Center for Studies of Venoms and Venomous Animals (CEVAP) of the São Paulo State University (UNESP) in partnership with the Vital Brazil Institute (IVB), Brazil, developed the apilic antivenom. For this, the principal toxins from the venom of Africanized honeybee maintained at the Lageado Experimental Farm, UNESP campus in Botucatu, São Paulo, Brazil, were extracted and purified. Next, previously selected horses were immunized with increasing doses of the chosen antigens. These protocols are described in detail in the developed guide for researchers and in the patent submitted [7, 11].

The proposed dose of the new antivenom was calculated taking into account the premises of the *WHO Guideline for the production control and regulation of snake antivenom immunoglobulins* [12] that prioritize the quantity of venom inoculated in the host, neutralization potency and the proposed antivenom dose. For these calculations, the authors relied on the fact that one bee inoculates during one sting approximately 0.1 mg of venom [1]. According to the serum neutralization tests, each milliliter of standardized antivenom neutralizes 1.25 mg of venom. Therefore, 10 mL of antivenom should neutralize the venom of 100 stings. The experimental validation of antivenom efficacy and preclinical tests are detailed in a paper in progress.

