### Objectives

Primary objectives: to evaluate the safety of the antivenom including number and severity of acute adverse events, as well as deaths suspected to be related to the intervention; and to confirm the lowest effective dose when faced with different quantities of venom inoculated in patients exposed to multiple stings from Africanized honeybees.Secondary objectives: to correlate the severity of the initial clinical condition with number of stings.Explanatory objectives: to evaluate the antivenom neutralizing power by pharmacokinetic and proteomic studies; and to evaluate the antivenom pharmacokinetics and immunogenicity.

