### Plan of treatment (specific, adjuvant, symptomatic and complementary)

#### Specific treatment

The *WHO Guideline for the production control and regulation of snake antivenom immunoglobulins* [12] suggests that the protocol prepared for the specific treatment be based on the estimated quantity of venom inoculated by the bee and on the neutralizing capacity of the antivenin. Thus, the authors suggested:Up to 5 stings: specific treatment is not indicated, except for a medical criterion.Between 5 and 200 stings: two vials of apilic antivenom.Between 201 and 600 stings: six vials of apilic antivenom.Above 600 stings: ten vials of apilic antivenom.

After the dose is determined by the attending medical team, the vials must be opened and their content aspirated by means of a syringe. Next, insert all the content into a flask containing 250 mL of normal 0.9% saline solution, previously emptied. This flask containing the antivenom must be connected into a Y formation with another flask containing 250 mL of 0.9% saline. One large-caliber vein of the forearm must be catheterized and these two contents need to be infused in the Y within two hours. All patients must be hospitalized and monitored throughout the infusion by the continuous presence of the hospital staff at the patient’s bedside. The team must also have at their disposal the drugs and equipment necessary for the treatment of mild or severe adverse reactions. Any adverse events and signs and symptoms of possible toxicity must be noted on the patient’s chart.

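### The dose rationale's own inputs give 125 stings per 10 mL of antivenom, not the stated 100, and no margin is declared

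*Protocol article*

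**What the plan says.** The section on antivenom development and dose proposal gives two inputs. The first is the venom load: "one bee inoculates during one sting approximately 0.1 mg of venom". The second is the potency found in neutralisation tests: "each milliliter of standardized antivenom neutralizes 1.25 mg of venom". It then draws the conversion from them: "Therefore, 10 mL of antivenom should neutralize the venom of 100 stings". The text shown mentions no safety factor, reserve or rounding.

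The Abstract and the section on specific treatment both say that dosing rests on the antivenom's neutralising capacity and on the number of stings or the venom they deliver. The dose itself is given in whole vials by sting band: "Between 5 and 200 stings: two vials of apilic antivenom", "Between 201 and 600 stings: six vials of apilic antivenom" and "Above 600 stings: ten vials of apilic antivenom". One part of the primary objectives is "to confirm the lowest effective dose when faced with different quantities of venom inoculated".

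**The concern.** The conversion is presented as the result of the two inputs, but it does not follow from them. A reader cannot tell whether 100 is a slip, a rounding or a margin that the authors chose.

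This would matter little in a background paragraph. Here it is the arithmetic behind the proposed dose, and the trial is meant to find how little antivenom is enough. If the reference point carries an unstated 25% excess, a statement that a given dose was or was not close to the minimum is hard to interpret. Later studies that reuse the conversion would carry the excess forward without knowing it.

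**Working it through.** **Inputs** (all from the section on antivenom development and dose proposal)
- Venom per sting: about 0.1 mg
- Potency: 1.25 mg of venom neutralised per mL
- Stated conversion: 10 mL for 100 stings

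**Trying to reproduce the stated figure**
- Stings neutralised = volume × potency / venom per sting
- 10 mL × 1.25 mg/mL = 12.5 mg of venom
- 12.5 mg / 0.1 mg = **125 stings**, not 100
- In reverse: 100 stings × 0.1 mg = 10 mg, and 10 / 1.25 = **8 mL**, not 10 mL

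**Size of the gap, with denominators**
- Volume above nominal need: 10 / 8 − 1 = 25%
- Nominal capacity left unused: 1 − 100 / 125 = 20%

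**What would give exactly 100**
- Venom per sting of 12.5 / 100 = 0.125 mg, or
- Potency of (100 × 0.1) / 10 = 1.0 mg per mL

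The article states neither value.

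**How far the word for approximately could stretch.** Assume, for illustration, that about 0.1 mg covers 0.05 to 0.15 mg. Then 10 mL covers 12.5 / 0.05 = 250 stings at one end and 12.5 / 0.15 = 83 at the other. The stated 100 lies inside that range, but so do many other figures. At the printed value the answer is 125.

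**Why vial count alone does not describe the dose relative to venom.** Within a band the number of vials is fixed, so capacity divided by load varies in inverse proportion to the sting count, whatever the vial volume.
- Two-vial band, from 6 stings (the Abstract enrols people with more than five) to 200: nominal load goes from 0.6 to 20 mg, a factor of 200 / 6 = 33
- Six-vial band, from 201 to 600 stings: nominal load goes from 20.1 to 60 mg, a factor of 600 / 201 = 3.0

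This spread comes from banding and not from the arithmetic error. It is shown only because it explains the second part of the fix.

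**The case against.** The strongest reply is that the sentence is loose but harmless. On the article's own inputs 10 mL does cover 100 stings, with capacity to spare, so as a lower bound the statement is true. The venom figure is approximate, and 0.125 mg, which gives exactly 100, rounds to 0.1 at one decimal. A cautious margin in a first human trial would also be reasonable. Treatment is fixed by band in whole vials, so a corrected sentence alters nobody's treatment.

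Most of this stands, and it sets the severity. It does not remove the point: the only printed value is 0.1, the text presents 100 as derived, and it declares no margin. If one was intended, a sentence saying so settles the matter.

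A second reply is that describing dose against venom load belongs to the analysis plan, and that the planned ELISA kinetics will measure circulating toxin and antivenom directly. That is fair. The ratio is offered as an inexpensive addition to reporting; its absence from the article is not a defect. It also inherits the uncertainty in 0.1 mg per sting.

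A reader might infer something stronger: that the bands under-dose at their upper limits, or that ten vials is too little for very large attacks. The article does not support this. The bounded bands reach 100 stings per vial at their limits (200 / 2 and 600 / 6), which matches the stated conversion if a vial holds 10 mL. The volume is not given, and an article may leave it to the full protocol or to the guide for researchers. Any claim of under-dosing would rest on an assumed volume.

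**Conclusion.** The point holds as a minor internal error. The two stated inputs give 125 stings per 10 mL, or 8 mL per 100 stings. The article's figure asks for 25% more antivenom than nominal need, equivalently leaving 20% of capacity unused, and does not say why.

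The arithmetic rests only on the printed 0.1 mg and 1.25 mg per mL and needs no further assumption. The direction is conservative: no under-dosing follows from this sentence, and no band, eligibility rule or endpoint changes. What is affected is the interpretation of the lowest-effective-dose objective, for which the conversion is the reference point. How large that effect would be cannot be judged from the article, since the distribution of sting counts among the 20 participants is unknown.

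**What to change.** 1. In the dose proposal, either correct the sentence to 125 stings per 10 mL (8 mL per 100 stings), or keep 100 and state that it is a deliberate margin of 25% above nominal need (20% of capacity unused), with the reason. Give the denominator, because 20% and 25% describe the same gap.
2. When reporting the lowest-effective-dose objective, describe each participant's dose by the following ratio as well as by number of vials: (mL given × 1.25 mg) / (stinger count × 0.1 mg). The stinger count is already made under complementary treatment.

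The cost is one sentence and one derived variable from data that the trial collects anyway. No dose, band or procedure changes. The small downside is that the ratio depends on the approximate 0.1 mg per sting, so it should be labelled nominal and read beside the measured venom and antivenom levels.

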### Design of the *Apis* study

This is a multicenter, non-randomized and open phase I/II clinical trial study to evaluate the safety, determine the pharmacokinetic and proteomic profile, and confirm the lowest antivenom dose, according to the severity of each case. It will include 20 adult individuals, of both sexes, afflicted with multiple stings from Africanized *Apis mellifera* honeybees. The study population will be of the type non-probabilistic by convenience (or accidental) sample, given the low demographic density of the studied phenomenon and the extreme geographic decentralization of this event. The sample size was estimated by considering examples of phase I/II clinical studies proposing to study the safety and neutralizing power and to confirm the minimum required dose of antivenom [12]. Not performing the sample calculation is justified by the fact that the efficacy outcome is not the target at this moment given that there are no data on safety and adequate dose. The study will last 36 months, with 24 months for recruitment.

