### Management of documents and publication policy

According to the law, all data obtained should be treated with discretion to ensure the privacy rights of the participant. The coordinating center must review the source document (case reports, charts and medical registries) for confirmation and registration. The research ethics committee (CEP) of each partner institution must approve the clinical research protocol, the the guide for researchers, the terms of free and informed consent (TFIC) and other information for the recruitment of patients, in addition to accompanying the conduction of the study. All the documentation (source documents, e-CRFs, laboratory exams, registries of medication dispensations in the study, correspondence related to the CEP and other annotations), must be kept on file for at least five years, in a location of restricted access. The coordinating institution undertakes to publish and disseminate the results obtained in an indexed peer-reviewed journal with a high impact factor. The choice of authors and collaborators will be based on the number of patients included, on the quantity of selection failures and on adherence to the procedures proposed. Moreover, if in the future any participating investigator wishes to use data from this study in publications or presentations, he or she will have to communicate such intention to the coordinating center 60 days prior to submission.

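### The plan fixes a convenience sample and states no rule for taking eligible victims in order, so selection of unknown direction and size may enter the improvement proportion and the adverse-event frequencies

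*Protocol article*

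**What the plan says.** The section on the design of the Apis study calls the trial a "multicenter, non-randomized and open phase I/II clinical trial study". On size and duration it says "It will include 20 adult individuals, of both sexes" and "The study will last 36 months, with 24 months for recruitment". On sampling it says "The study population will be of the type non-probabilistic by convenience (or accidental) sample, given the low demographic density of the studied phenomenon", and gives as a second reason "the extreme geographic decentralization of this event". The sample size was not calculated: "Not performing the sample calculation is justified by the fact that the efficacy outcome is not the target at this moment".

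The Outcomes section lists two primary outcomes: a safety profile built on laboratory and clinical adverse events, and the proportion of participants whose initial clinical picture improves. No control group or reference rate is described.

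The Inclusion and Exclusion lists say who may enter. They do not say that every eligible victim at an active centre is offered entry, or in what order. Selection failures appear once, under the publication policy: "The choice of authors and collaborators will be based on the number of patients included, on the quantity of selection failures and on adherence".

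**The concern.** The reasons given for a convenience sample rule out only a probability sample. A consecutive series is also non-probabilistic and copes equally well with rare, scattered events. The plan therefore commits to a sampling method without justifying it against the obvious alternative.

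This matters because of the rest of the design. Treatment is open, there is one group, and whoever offers participation can already see how ill the victim is. If that influences who is approached, the case mix of the 20 shifts, and with it the improvement proportion and the frequency of adverse events. No comparison arm absorbs the shift. Without a report of eligible victims who were not entered, a reader of the results cannot tell whether it occurred. Those victims cannot be recovered at the analysis stage if nobody recorded them.

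**Working it through.** The plan's figure of 20 cannot be reproduced, because no rate, power or precision target is given. Three checks are possible.

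**1. Does the stated reason support the choice?**
- Low density and dispersion mean no sampling frame, hence no probability sample. This follows.
- Low density and dispersion mean eligible victims at an active centre are not taken in order. This does not follow: order of arrival needs no frame.

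**2. Is there room for selection?** Inputs come from the Background section: "in 2015 this number grew to 13,597 cases with 39 deaths", with moderate cases at 10–18% and severe cases at 0.8–1.3%.
- Enrolment needed: 20 / 24 = 0.83 per month over all centres.
- National reports in 24 months at the 2015 level: 13,597 × 2 = 27,194.
- Moderate plus severe: 27,194 × (0.10 + 0.008) = 2,937, to 27,194 × (0.18 + 0.013) = 5,248.
- If active centres see 1% to 10% of these (an assumption; capture is not given): about 29 to 525 candidates for 20 places.

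The national counts cover all ages and do not separate single from multiple stings. Minors, pregnant women, people with chronic disease and refusals have not been removed. At the low end the candidates could fall below 20, which would leave nothing to select from. At the high end there would be ample room.

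**3. What could selection do?** Let k be the enrolment rate of victims who would do badly, relative to the others. No value of k is in the documents; those below are assumed.
- Observed improvement for true proportion p: p / (p + (1 − p)k).
- Observed adverse-event proportion for true proportion q: qk / (qk + 1 − q).

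| k | True improvement 80% reads | True adverse-event proportion 30% reads |
|---|---|---|
| 0.5 | 0.8/0.9 = 88.9% | 0.15/0.85 = 17.6% |
| 0.8 | 0.8/0.96 = 83.3% | 0.24/0.94 = 25.5% |
| 1.0 | 80.0% | 30.0% |
| 1.5 | 0.8/1.1 = 72.7% | 0.45/1.15 = 39.1% |

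The sign depends on whether k is below or above 1, and k need not be the same for the two outcomes. For scale, 16 improved out of 20 (80%) has an exact 95% interval of 56.3% to 94.3%. The illustrated shifts in improvement are smaller than the sampling error, but the interval does not account for them. Consecutive entry would leave the precision unchanged and remove only the selection term.

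**The case against.** The strongest reply is that the concern is read from silence. The article adds the word accidental, which can mean taking cases as they present, and an article may leave the enrolment procedure to the full protocol. This is also a 20-person phase I/II study that openly declares its sampling and disclaims efficacy as its target, so the main loss is generalisability.

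Part of this stands. Several stronger readings are tempting, and the documents do not support them:
- *That investigators are permitted to pick among eligible victims.* No text says so; it is an inference from the lack of a rule.
- *That both primary outcomes are biased proportions.* Only improvement is worded as a proportion; safety is an adverse-event profile.
- *That the results will look too favourable.* The article says no specific treatment exists, so clinicians might equally favour sicker victims (k above 1). Nor does any passage link serum hypersensitivity to looking ill on arrival.
- *That the authorship rule rewards easy cases.* It does not say whether selection failures count for or against a centre.
- *That consecutive enrolment is shown to be feasible.* Number of centres, case flow and acute consent are not quantified.

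What does not stand is the suggestion that nothing is fixed. The sampling method is an affirmative statement with a reason attached, and the reason does not cover it. Disclaiming efficacy does not help either: improvement is listed as primary, and safety, which is a target, carries the same selection. If accidental means as they present, the change merely says so.

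**Conclusion.** The concern holds in a limited form. The article fixes a convenience (or accidental) sample, shows no requirement to take eligible victims in order, and justifies only the absence of a probability sample. Selection may therefore enter the single-group improvement proportion and the adverse-event frequencies. Its direction and size cannot be judged from the documents. The range of 73% to 89% for a true 80% improvement is an illustration under assumed enrolment ratios of 1.5 to 0.5, not an estimate.

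The weight is moderate. No figure in the plan is wrong and no test is invalidated, but the primary results would describe an enrolled group whose relation to the eligible victims is unknown. Consecutive entry is a less selective method and plausible at 0.83 enrolments per month. If case flow is thin, nearly every eligible victim is needed anyway and the rule costs little; if flow is ample, the rule matters.

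**What to change.** - **Design of the Apis study:** replace the convenience sample by consecutive entry. Victims who meet the entry criteria are offered participation in order of presentation at each activated centre while recruitment is open, until 20 are enrolled. The criteria should include the condition of more than five stings, which stands in the Abstract but not in the Inclusion list. The two must be reconciled first; applied alone, the Inclusion list would admit victims with five stings or fewer.
- **Log:** each centre keeps an anonymous list of eligible victims not enrolled, with sting band and reason.
- **Reporting:** give the counts by sting band beside both primary outcomes, and describe both as estimates for the enrolled case mix.
- **Publication policy:** state that selection failures are not held against a centre when authorship is decided.

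The cost is a wording change, which has to pass the ethics committees, and one log line per victim not enrolled. There are no added participants, procedures or follow-up.

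There are two small downsides. Centres lose discretion over whom to approach. High sting bands may also hold few participants, which bears on the objective of confirming dose across venom quantities. On the national mix, 20 consecutive cases would include about 0.2 to 0.3 severe (20 × 0.008 to 0.013) and 2 to 3.6 moderate (20 × 0.10 to 0.18). That mix covers all reported stings, so it is only a rough guide to victims with more than five. A convenience sample does not guarantee a better spread. The number enrolled per band should be reported.

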### Outcomes

Primary outcomes: to evaluate the antivenom safety profile through laboratory and clinical adverse events; to verify the proportion of individuals with improvement in the initial clinical picture by monitoring signs, symptoms and laboratory exams.Secondary outcomes: to evaluate the degree de correlation between the number of stings and the severity of the initial clinical picture (APACHE II).Exploratory outcomes: to evaluate the pharmacokinetic and immunogenic profile of antivenom/venom at doses established by an analysis of the blood samples collected at different moments (before and at 2, 6, 12 and 24 h after heterologous serum therapy); to evaluate the proteomic profile of the antivenom as determined by the differential expression of the proteins albumin, C-reactive protein (CRP) and fibrinogen, by the presence of the components melittin and phospholipase A_2_, and by the heterologous serum protein profile of the degradome and peptide/protein biomarkers.

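### The sample size is excused because efficacy is not a target, yet improvement is a primary outcome and the lowest effective dose a primary objective, and the design can support neither

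*Protocol article*

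**What the plan says.** All references are to the protocol article.

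- **Design of the Apis study.** The trial is open, multicenter and non-randomized. "It will include 20 adult individuals, of both sexes". On the basis for that number: "The sample size was estimated by considering examples of phase I/II clinical studies". The reason for making no calculation is that "the efficacy outcome is not the target at this moment given that there are no data on safety and adequate dose".
- **Objectives.** Safety is a primary objective. So is confirming the lowest effective dose across different amounts of inoculated venom.
- **Outcomes.** One primary outcome is the safety profile. The other is "to verify the proportion of individuals with improvement in the initial clinical picture by monitoring signs, symptoms and laboratory exams".
- **Stated aims.** The abstract's conclusions call the protocol "designed specifically to evaluate the preliminary efficacy and safety of a new antivenom". The end of the Background and the article's Conclusions also name preliminary efficacy as something to be evaluated.
- **Specific treatment.** Each sting band has one vial count: two for 5 to 200 stings, six for 201 to 600, ten above 600.
- **Adjuvant and symptomatic treatment.** Fluids, vasoactive drugs, antihistamines, corticosteroids, adrenaline, analgesia and bronchodilators are provided for alongside the antivenom.
- **Background.** Direct venom toxicity is tied to a large number of stings, "generally more than 200 in adults".

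**The concern.** The reason given for 20 participants is that efficacy is not being targeted. The outcome list contradicts that reason, so the size is left without a justification that fits what the trial says it will measure.

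What the trial may conclude is also at stake. A primary outcome reported as, say, 18 of 20 improved, in a protocol that announces preliminary efficacy as an aim, invites the reader to credit the antivenom. With no comparator and active co-treatment, that inference is not available. The same number might also be offered as confirming that the chosen doses are the lowest effective ones, a question this design does not address.

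**Working it through.** **1. The plan's own figure.** The 20 cannot be reproduced or refuted. It was set by precedent, and no alpha, power, effect size or reference rate is stated.

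**2. The passages side by side.** The design section says efficacy is not the target. The Outcomes section has a primary outcome with efficacy content (proportion improved). The Objectives section has a primary objective with efficacy content (lowest effective dose). The reason given for making no calculation therefore does not hold for two of the items labelled primary.

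**3. Can improvement be attributed to the antivenom?** There is no described control arm and no stated reference rate, and other active drugs are given at the same time. An observed proportion mixes natural course, supportive care and any antivenom effect.

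Treatment starts above five stings, whereas the Background places direct toxicity generally above 200. Part of the 5 to 200 band may therefore have little direct toxicity for the antivenom to reverse.

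**4. Can the lowest effective dose be confirmed?** Vial count is fixed by band, so no two doses are planned at the same venom load. Comparing bands compares different doses and different venom loads together. Even if improvement were attributable, it would show at most that the dose given was enough, not that a smaller one would have failed.

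**5. What a high proportion would mean with no drug effect.** Let p be the improvement rate without antivenom. It is not in the document, so it is assumed over a range. For 20 participants:

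P(at least 18 improve) = 190·p^18·(1−p)^2 + 20·p^19·(1−p) + p^20

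| Assumed p | Terms | P(≥18 of 20) |
|---|---|---|
| 0.90 | 0.285 + 0.270 + 0.122 | 0.68 |
| 0.80 | 0.137 + 0.058 + 0.012 | 0.21 |
| 0.70 | 0.028 + 0.007 + 0.001 | 0.04 |

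The exact (Clopper-Pearson) 95% interval for 18/20 is 68.3% to 98.8%. For 20/20 it is 83.2% to 100%, with lower limit 0.025^(1/20) = 0.832. So even a perfect result cannot exclude a background rate of 0.90. It could exclude 0.80, since 0.80^20 = 0.012. The reading of the outcome depends on a rate that the document does not give.

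**6. What 20 participants give for safety.**

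- Upper limit of the two-sided exact 95% interval after 0/20 events: 1 − 0.025^(1/20) = 0.168, that is 16.8%.
- Chance of at least one event when true incidence is 5%: 1 − 0.95^20 = 0.64.

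**The case against.** **Points that stand.** A first-in-human study of 20 patients needs no power calculation, and choosing the number by precedent is coherent. Saying the size was estimated from examples and also that no calculation was made is not a contradiction. The abstract and the Conclusions state aims but designate nothing as primary; only the Objectives and Outcomes sections do. The exploratory venom and antivenom kinetics may carry some information on neutralization, so it would be too strong to say that the trial can tell us nothing about efficacy. A condensed article may leave the definition of improvement to the full protocol, and its absence is not raised here.

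**Stronger readings the document does not support.**

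- A reader might take "Asymptomatic and mild envenomation accounted for up to 90% of cases" to mean that most participants recover anyway, and so expect 18 of 20 to improve on an inert product. That figure is a severity class among all reported bee-sting cases, and the Background itself warns that single and multiple stings were not separated. It is not a recovery rate, and it does not describe a sample with more than five stings.
- A reader might use the severe share (0.8 to 1.3%) to conclude that the six- and ten-vial groups will probably be empty: 0.992^20 = 0.85 and 0.987^20 = 0.77. Vials follow sting count, not severity class, and no link between the two is given. Adding the moderate class (10 to 18%) gives 10.8 to 19.3% and a chance of 0.892^20 = 0.10 to 0.807^20 = 0.01. A figure that moves this far with an unproven mapping cannot carry the claim.
- The 200-sting statement is qualified as general. It does not say that direct toxicity is absent below that count.

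None of this removes the conflict between the sections or the attribution problem, since neither depends on a recovery rate.

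**Conclusion.** The point holds as a contradiction in the text with a consequence for inference. The justification for 20 participants denies an efficacy target that the primary outcome and a primary objective both contain. As designed, the improvement proportion cannot be attributed to the antivenom and cannot establish a lowest effective dose. This conclusion rests on the described design (open, no comparator or reference rate, co-treatment, one vial count per band), not on any assumed recovery rate.

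The size of the interpretive risk does depend on an assumption. The chance of at least 18 of 20 improving with no drug effect runs from 0.04 to 0.68 as the background rate goes from 70% to 90%. Without a stated reference rate the plan cannot say where in that range it lies.

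**What to change.** 1. **Outcomes.** Make safety the primary outcome. Move the proportion improved to a descriptive secondary outcome with an exact interval, reported by sting band and for participants with more than 200 stings.
2. **Sample-size text.** Justify 20 by the safety precision in step 6 of the working, in place of the statement that efficacy is not the target.
3. **Objectives.** Reconcile the lowest-effective-dose objective with the design section. If only the outcome list is changed, that objective is left primary with no primary outcome behind it. It should not be concluded from the uncontrolled proportion.
4. **Aims.** Align the preliminary-efficacy wording in the abstract, the Background and the Conclusions, so that efficacy is not claimed from that proportion either.

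The total stays at 20, and treatment and data collection are unchanged. The cost is rewording and a more modest claim.
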